#### Anxiety levels

*State-Trait Anxiety Inventory (STAI)* [40]. The two forms of anxiety (state and trait) are separated in the inventory, and both have their own 20 separate questions. The questionnaire is therefore composed of 40 items ranging from 0 (almost never) to 4 (almost always). The score ranges from 0 to 80 points. For both forms, higher scores indicate higher levels of anxiety.

#### Eye movement tasks

*Fixation task* [31]. The participant is asked to look at a centred fixation dot (diameter of 0.5 degrees) for 1 min (Fig. 1a). The task comprises three trials with a short resting period between them.

**Fig. 1 Fig1:**
[figure not shown]
Eye-tracking tasks. **a** Fixation task, **b** Prosaccade/Antisaccade task, **c** Memory-guided task

*Prosaccade/antisaccade task* [35]. Each trial begins with a centred fixation cross (random period 1000–3000 ms) followed by a dot (diameter of 0.5 degrees) that appears in a random location either 8º left or right of the fixation cross (1000 ms). In the prosaccade condition the participant is required to direct her gaze towards the dot as quickly as possible, while in the antisaccade condition the participant is required to direct her gaze to the opposite position of the dot (Fig. 1b). First, participants are required to complete a practice phase consisting of five prosaccade trials and five antisaccade trials. Once practice trials are completed, a total of 240 trials are presented organized in five blocks as follows: 60 prosaccades; 40 antisaccades; 40 antisaccades; 40 antisaccades; 60 prosaccades (Fig. 1b).

*Memory-guided saccade task* [33]. The participant is asked to look at a centred fixation cross for a random period from 1000 to 3000 ms. Next, a 50 ms-dot (diameter of 0.5 degrees) is presented in a random location in the periphery (5–10° left or right) while the central fixation remains for a random period in the interval 1000–3000 ms. The participant is instructed to keep her eyes on this central fixation during the entire delay and to trigger a saccade towards the memorised location of the peripheral dot as soon as the central fixation disappears. First, participants are required to complete a practice phase consisting of eight trials. Once practice trials are completed, a total of 52 trials are presented, with an equal number of target presentations for each peripheral location (Fig. 1c).

For all the tasks: cross fixation colour, font type and size (RGB: 255,255,255; Font: Times New Roman, 28). Background screen colour (RGB: 51,51,51).

### Other measures

Age, socioeconomic status, and highest level of education completed will be collected as sociodemographic variables. BMI will be measured and computed according to population norms and adjusted for age, sex, and height.

### Data analysis

Eye-tracking data will be analysed with SR Research’s program DataViewer and Microsoft Excel. See Table 1 for a detailed overview of the outcome measures associated with the eye-tracking data. The proportion of participants and excluded trials, and the percentage of lost data will be reported.

**Table 1 Tab1:** Outcome measures associated with the eye-tracking data

Task	Outcomes		
Fixation	Rate of SWJs. Threshold for SWJ detection included saccade pairs (an initial saccade that moves the fovea away from the cross fixation, followed by a second saccade in the opposite direction to refoveate the fixation) within 200 ms, with amplitudes between 0.1° and 5°		
Prosaccade	Gain, latency, and peak velocity of correct saccades	Errors	*Anticipation rate* making a saccade during the fixation period, prior to the presentation of the target dot or within 80 ms of its presentation
			*Prosaccade error* saccade in the opposite direction of the peripheral stimulus
Antisaccade	Gain, latency, and peak velocity of correct saccades	Errors	*Corrected error rate* looking at the target, then looking at the correct location at the mirror image of the target
			*Latency of the correction saccade* how long it took to make a saccade in the correct direction following the incorrect saccade
			*Uncorrected error rate* looking at, instead of away from, the target
			*Anticipation rate* making a saccade during the fixation period, prior to the presentation of the target dot or within 80 ms of its presentation
Memory-guided saccade	Gain, latency, and peak velocity of correct saccades	Errors	*Inhibitory errors* Looking at the dot when it was presented or making a saccade before the response period
			*Directional errors* Looking in the wrong direction to where the stimulus had been presented during the response time

Practice trials are aimed to acquaint the participant with the experimental paradigms and will not be statistically analyzed. In the saccade tasks, saccades smaller than 2° will not be analyzed. The error rate for each participant will be calculated as the proportion of erroneous trials to all valid trials. The gain of the first saccade will be calculated as a ratio of the first saccade amplitude divided by the desired saccade amplitude (e.g., 8° for Prosaccade task). Latency of the first saccade is defined as the latency from appearance of the target to the start of the saccade

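### Peak velocity is compared between groups without allowing for saccade amplitude, so a difference in gain can appear as, or hide, a difference in velocity

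*Protocol article*

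**What the plan says.** In the protocol article, Table 1 (Data analysis) gives "Gain, latency, and peak velocity of correct saccades" as outcomes for the prosaccade, antisaccade and memory-guided tasks. Velocity is thus 3 of the 18 outcomes listed there.

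Amplitude is used in two places only. Gain is the "ratio of the first saccade amplitude divided by the desired saccade amplitude (e.g., 8° for Prosaccade task"), and there is a size floor: "In the saccade tasks, saccades smaller than 2° will not be analyzed". Neither is linked to velocity.

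Under Eye movement tasks, the prosaccade/antisaccade dot "appears in a random location either 8º left or right of the fixation cross". The memory-guided dot "is presented in a random location in the periphery (5–10° left or right"), and "a total of 52 trials are presented, with an equal number of target presentations for each peripheral location".

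The Statistical analysis section tests group differences by t-test or Wilcoxon test with a correction for multiple comparisons. Premorbid intelligence and anxiety enter as covariates only after a significant difference. The section also correlates the Table 1 outcomes with S-EDE-Q, STAI and BMI. Amplitude and gain are not named as covariates anywhere.

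**The concern.** Peak saccade velocity increases with saccade amplitude. The article does not say so; it is general knowledge of the measure. At a fixed 8° target, gain and amplitude are the same quantity up to a constant, so the comparison of raw mean velocity partly repeats the comparison of gain.

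This can mislead in two directions. A group that undershoots will look slow although its saccades have normal speed for their size. A group that is truly slower but makes longer saccades may show no difference. The planned covariates cannot separate these cases, because neither of them is amplitude. The correlations of raw velocity with symptom scores have the same weakness.

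What is at stake is the reading of one set of parameters in a search for eye-movement abnormalities: one phenomenon could be reported as two, or a real one missed.

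**Working it through.** **The plan's own figure.** For d = 0.8, two-sided alpha 0.05 and 26 per group, the noncentrality is 0.8 × √(26/2) = 2.88 on 50 degrees of freedom. Power is 0.807; with 25 per group it is 0.791. The stated 26 per group reproduces, and nothing below changes it.

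**Inputs from the article.** Target at 8°; gain = amplitude / target distance; 26 per group; alpha 0.05.

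**Assumptions (not in the article).** A saturating curve V = Vmax × (1 − exp(−A/c)), four parameter pairs, baseline gain 0.95, between-subject SD of 40 to 80°/s, and the same curve in both groups, that is, no velocity abnormality.

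**Effect of gain at 8°.** Gains of 0.95, 0.90 and 0.85 correspond to amplitudes of 7.6°, 7.2° and 6.8°. For Vmax = 500 and c = 6:

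- V(7.6) = 500 × (1 − exp(−1.267)) = 359.1°/s
- V(7.2) = 500 × (1 − exp(−1.200)) = 349.4°/s
- V(6.8) = 500 × (1 − exp(−1.133)) = 339.0°/s

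The differences are 9.7 and 20.1°/s. For all four pairs:

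| Vmax, c | Gain difference 0.05 | Gain difference 0.10 |
|---|---|---|
| 500, 4 | 7.9°/s | 16.6°/s |
| 500, 6 | 9.7°/s | 20.1°/s |
| 500, 10 | 9.5°/s | 19.5°/s |
| 600, 14 | 10.1°/s | 20.5°/s |

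Dividing by the SD:

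- Gain difference 0.05: d from 7.9/80 = 0.10 to 10.1/40 = 0.25. The chance of p < 0.05 is about 6% to 15%.
- Gain difference 0.10: d from 16.6/80 = 0.21 to 20.5/40 = 0.51. The chance of p < 0.05 is about 11% to 44%.

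These chances are before any multiplicity correction; the nominal level is 5%.

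**Effect of target mix in the memory-guided task.** As presented, each location occurs equally often, so the expected shift is zero. For an extreme case, suppose targets at 5° and 10° only and gain 0.9 (amplitudes 4.5° and 9.0°), and let trial loss in one group reduce its share of 5° targets. The shift is (0.50 − share) × [V(9.0) − V(4.5)]:

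- Share 45%: about 5.5 to 6.2°/s, d about 0.07 to 0.16.
- Share 40%: about 11.0 to 12.5°/s, d about 0.14 to 0.31.

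The 2° floor can contribute little. It removes only saccades with gain below 2/5 = 0.4 at a 5° target and below 2/10 = 0.2 at a 10° target.

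**The case against.** Most of the case on the other side concerns size and importance.

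- **Gain is reported beside velocity in every task.** An undershooting group would be visible as such, and a velocity difference with equal gain can be read as it stands. This is fair. A reader might infer that raw velocity can show nothing about saccade dynamics; that goes too far. But comparing group means of gain by eye does not remove its contribution when gain does differ.
- **Target distance is balanced.** A reader might infer from the 5–10° range that the groups face different target mixes. The article does not support this: prosaccade/antisaccade targets are fixed and memory-guided locations are presented equally often. A difference could arise only if trial loss depends on eccentricity and does so differently by group. More inhibitory errors are hypothesised in the subclinical group, so unequal loss is plausible, but nothing shows that it would depend on eccentricity. The article also undertakes to report excluded trials and lost data.
- **Velocity is peripheral.** The hypotheses concern latency, inhibitory errors and square wave jerk rate; the discriminant analysis uses square wave jerk rate and anxiety. The study calls itself exploratory, and nothing singles out velocity as a candidate biomarker. This stands and limits the weight of the point.
- **The size is assumed, and no gain difference is hypothesised.** True; hence the ranges. The planned correction would also make false positives rarer. If it were Bonferroni over 18 outcomes (the method is not named; level 0.05/18 = 0.0028), the chance for d of 0.21 to 0.51 falls to about 1% to 11%. It does not remove the bias in the estimate.
- **A full protocol or analysis plan might add an adjustment.** Possible. But the article states the group test and names its covariates, and amplitude is not among them.

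**Conclusion.** The point holds in limited form. The stated analysis compares peak velocity in three tasks without accounting for amplitude, so a group difference in gain can produce or mask a velocity difference. At the 8° target the shift is about 8 to 21°/s, or d about 0.1 to 0.5, for a gain difference of 0.05 to 0.10. This rests on the assumed curves, the assumed SD of 40 to 80°/s and a gain difference that the article does not predict. It is below the design effect of d = 0.8.

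In the memory-guided task, target distance adds to this only if the retained correct trials differ in eccentricity between groups. A reader might also infer that the study's main conclusions are compromised. They are not: velocity is an exploratory, non-hypothesised outcome, and no main hypothesis or sample size figure depends on it. The case for a change is that it is cheap and gives a clearer answer.

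**What to change.** Compare peak velocity between groups adjusted for amplitude. The preferred form is a trial-level mixed model, run separately for each task over the correct saccades: log peak velocity on group and log amplitude, with a participant random effect. The group coefficient is then the velocity difference at equal amplitude, and it takes the place of the velocity t-test within the planned multiplicity correction. Report raw mean peak velocity descriptively beside gain. For the memory-guided task, also show the retained correct trials by eccentricity and group.

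Use a common slope for amplitude. Separate slopes for each participant may be imprecise where all targets lie at 8° and amplitudes vary little within a person.

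The cost is slightly more processing and a less direct comparison with raw velocities in earlier studies. Amplitude is already needed for gain, so no new data are required, and the sample size stays at 26 per group.

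### As written, memory-guided saccade latency is timed from the dot rather than the go signal, so it includes the random 1000–3000 ms delay

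*Protocol article*

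**What the plan says.** In the protocol article, Data analysis, the text under Table 1 defines latency once for the saccade tasks: "Latency of the first saccade is defined as the latency from appearance of the target to the start of the saccade". No task is excepted. Table 1 lists "Gain, latency, and peak velocity of correct saccades" as outcomes of the prosaccade, antisaccade and memory-guided conditions alike.

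Under Eye movement tasks, the memory-guided task shows a peripheral dot for 50 ms "while the central fixation remains for a random period in the interval 1000–3000 ms". The participant has to keep looking at the centre through that delay and then "trigger a saccade towards the memorised location of the peripheral dot as soon as the central fixation disappears". The same paragraph uses the word target for the dot: "a total of 52 trials are presented", "with an equal number of target presentations for each peripheral location". In this task, therefore, appearance of the target means dot onset, and the signal to move comes 1 to 3 seconds later.

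In the prosaccade and antisaccade conditions, dot onset is itself the signal to move, so the rule fits them.

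**The concern.** A latency outcome should measure how quickly the participant responds once she is allowed to. Under the written rule, a correct memory-guided trial is scored as a computer-generated waiting time averaging 2000 ms plus the reaction time. The waiting time carries no information about the participant.

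Two consequences need to be kept apart.

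- **Noise.** Random variation in the delay passes into each participant's mean and weakens the group comparison. It also weakens the exploratory correlations with S-EDE-Q, STAI and BMI planned under Statistical analysis.
- **Possible selection.** Latency is taken from correct saccades only, and a saccade made before the response period counts as an inhibitory error. If long delays produce more such errors, the group that makes more of them keeps a shorter average delay. It would then appear faster with no true difference.

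**Working it through.** **Inputs from the protocol article**
- Delay: random, 1000–3000 ms; 52 memory-guided trials (Eye movement tasks).
- d = 0.8, α = 0.05, power 80%, 26 per group (Sample size calculation).

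**Assumptions, because the protocol does not give them**
- Delays are independent and uniform on the interval.
- The between-participant SD of the properly timed mean latency, s, lies between 30 and 150 ms.
- Inhibitory-error rates, and how they depend on delay, are as stated in step 4.

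**1. The plan's own figure.** A two-sided independent-samples t-test (noncentral t) with d = 0.8 and 26 per group has power 0.807, so 26 per group reproduces. A one-sided test would need only 21, so the plan is evidently two-sided.

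**2. Noise from the delay.**
- Per trial: SD = 2000/√12 = 577 ms.
- On a participant's 52-trial mean: 577/√52 = 80 ms. With lost trials it is larger: 577/√40 = 91 ms and 577/√30 = 105 ms.
- On the group difference, from the delay alone: SE = 80 × √(2/26) = 22 ms.

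**3. Effect on power.** The diluted effect is d_eff = 0.8 × s/√(s² + 80²), with 26 per group and two-sided α = 0.05.

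| Assumed s (ms) | d_eff | Power |
|---|---|---|
| 30 | 0.28 | 0.17 |
| 50 | 0.42 | 0.32 |
| 80 | 0.57 | 0.52 |
| 100 | 0.62 | 0.60 |
| 150 | 0.71 | 0.70 |

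Timed from fixation offset, the 80 ms term disappears and power returns to 0.81.

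**4. Bias.** Suppose premature saccades occur at a constant hazard h per second from dot onset. For delays of 1 to 3 s, the retained fraction is (e^(−h) − e^(−3h))/(2h), and the mean retained delay is 1 + 1/h − 2/(e^(2h) − 1) seconds.
- h = 0.1: 18.0% errors, mean retained delay 1.967 s.
- h = 0.2: 32.5% errors, mean retained delay 1.934 s. The difference from h = 0.1 is 33 ms.

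Simulation used 26 per group, 52 trials, s = 50 ms, no true latency difference and 4000 repetitions:

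| Error rates, group 1 vs group 2 | Mean latency difference, group 2 − group 1 | Type I error |
|---|---|---|
| 20% vs 20% | about 0 ms | 0.05 |
| 10% vs 20% | about −20 ms | 0.11 |
| 20% vs 30% | about −22 ms | 0.11 |
| 20% vs 40% | about −49 ms | 0.35 |

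The shift therefore comes from unequal, delay-dependent exclusion. The random delay by itself does not move the group difference.

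**The case against.** The strongest reply is that this is a generic note that was not adapted to one task. Its gain example is explicitly for the prosaccade task, and Table 1 refers to a response period in the memory-guided task, so the authors do recognise a phase after the delay. Values near 2 s would expose the wrong anchor on first inspection. Latency could then be recomputed, since the task itself generates the offset time. All of this is fair and lowers the severity. It does not remove the error: a definition is stated, and for this task it gives the wrong quantity.

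The second reply is that no hypothesis depends on it. Under Study objectives and hypothesis, shorter latency is assigned to the prosaccade/antisaccade task and inhibitory errors to the memory-guided task. The definition of inhibitory errors does not use latency, and SWJ rate and the discriminant analysis are untouched. This stands.

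The third reply concerns the figures, and it also stands.
- If delays come from a balanced or common list, the 80 ms shrinks or vanishes.
- The protocol gives no value for s.
- The d = 0.8 was chosen for a generic t-test, not for this outcome.

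A reader might go further and infer that latency is wrongly defined in every task, or that the group comparison is biased as a matter of course. The protocol supports neither. The fixation task has no latency outcome, correction-saccade latency has its own definition, and the prosaccade and antisaccade conditions are correctly anchored. Both groups draw delays by the same rule, so bias needs unequal error rates and errors that rise with delay. The protocol hypothesises the first but says nothing on the second. Inhibitory errors also include looking at the dot as it is shown, which cannot depend on how long the later delay lasts. If all errors were of that kind, the selection effect would be zero.

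**Conclusion.** The concern holds for one variable. Read as written, memory-guided latency of correct saccades is the imposed delay plus the reaction time. That follows from the text alone and needs no assumed number.

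The size is conditional. With independent uniform delays the added SD is about 80 ms on a 52-trial mean. For a true d = 0.8, power is about 0.17–0.70 instead of 0.81 across assumed s of 30–150 ms: a severe loss at the low end and a modest one at the high end. Bias is possible but not established: zero if error rates are equal or errors occur at dot onset, and about 20–50 ms in the assumed delay-dependent scenarios.

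The outcome is listed but not specifically hypothesised, in a study that describes itself as exploratory, and the harm can be undone from the recorded timings. This is a definition to correct before analysis. It does not undermine the main comparisons.

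**What to change.** Replace the single rule with a rule for each task. For prosaccade and antisaccade, keep latency from target onset to the start of the first saccade. For the memory-guided task, define latency from disappearance of the central fixation to the start of the first analysable saccade, applying the protocol's existing 2° minimum.

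The cost is one sentence. The task already controls the moment of fixation offset, so no new procedure, equipment or participants are needed. If data have already been processed under the written rule, memory-guided latency can be recomputed from the recorded event times.

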### Sample size calculation

An 80% of power analysis and a significant criterion of α = 0.05 were set since these are considered a convention for general use specifically in the psychology field [41, 42]. Regarding the effect size, based on previous literature on the topic [34], we choose a large effect size (d = 0.8) [41]. Thus, a priori t-test G*Power v3.1.9.2 (Dusseldorf University, Germany, http://www.gpower.hhu.de/en.html) analysis yields a minimum sample of 26 participants in each group (N = 52, two groups: participants with subclinical ED symptomatology vs. control participants). Nevertheless, if significant results were not obtained after completion of the study, a retrospective power analysis will be carried out with the participants responses to verify whether the non-significant result is due to lack of relationship between the groups or due to lack of statistical power. In this case, more participants will be recruited.

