### Study objectives and hypothesis

As Malcom and Phillipou [18] noted in their recent review, demonstrating a relationship with illness is one of the first steps in determining biomarkers and endophenotypes. As illustrative example, first Phillipou et al. [33] showed the existence of specific eye movement anomalies in patients with AN and only after these findings, they amplified the scope of their study and were able to identify the state-independence of these eye movement abnormalities [32]. Following this line of reasoning, we will investigate whether the aforementioned eye movement abnormalities detected are, in this case, associated in young-adult women with subclinical symptomatology. Therefore, this study will take as primary aim to investigate whether participants with subclinical ED symptomatology and control participants differ in their performance on a range of eye movement tasks. We hypothesize that participants with subclinical ED symptomatology compared to controls would be prone to show shorter saccade latencies and more inhibitory errors in a prosaccade/antisaccade task and in a memory-guided saccade task, respectively, and an increased rate of SWJs in a fixation task. Additionally, as secondary aim, and following the same approach of Phillipou et al. [31, 32], we will test the potential role of SWJ rate and anxiety for discriminating the different groups tested in our study (participants with subclinical ED symptomatology vs. control participants).

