### Statistical analysis

Statistical analyses will be performed with SPSS v.28. Normality and outliers will be checked through graphic tests such as QQ plots, histograms, and box plots. Cronbach’s α for each questionnaire will be reported. Group analyses will be performed with Student's t-test paired comparison (for normal distribution) or Wilcoxon tests (for non-normal distribution). We will apply a correction for multiple t-test comparisons. Cohen’s d will be reported for variables showing significance. In case of significant differences between study groups, we will then include confounding variables (premorbid intelligence and anxiety) as covariates in the analysis described above. Across groups, exploratory Pearson's correlation analyses will also be conducted between S-EDE-Q, STAI scores, and BMI and the outcome measures associated with the eye-tracking data (see Table 1, for a detailed view). Additionally, if significant differences are found between STAI scores and SWJ rate, consistent with previous literature [31, 32], a discriminant analysis will be performed on the entire sample to elucidate to what extent both measures correctly classify group membership (participants with subclinical ED symptomatology vs. control participants). Alpha will be set at 0.05 for all analyses.

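### The stated 80% power applies to one uncorrected test at 0.05, but the plan corrects across several outcomes with none named primary, so power per outcome is below 80%

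*Protocol article*

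**What the plan says.** Three places in the protocol article bear on this.

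- *Sample size calculation.* The section sets "An 80% of power analysis and a significant criterion" of 0.05, and then "we choose a large effect size (d = 0.8"). The a priori t-test "analysis yields a minimum sample of 26 participants in each group (N = 52"). No outcome is attached to this calculation and no allowance is made for multiple testing.
- *Statistical analysis.* "We will apply a correction for multiple t-test comparisons". Neither the method nor the set of tests it covers is given. The section closes with "Alpha will be set at 0.05 for all analyses".
- *Study objectives and hypothesis.* The primary aim is whether the groups "differ in their performance on a range of eye movement tasks". Directional predictions are then made for square wave jerk (SWJ) rate, for latency in the prosaccade/antisaccade task and for inhibitory errors in the memory-guided task. That is three outcomes, or four if prosaccade and antisaccade latency are counted separately. None is called primary.

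Table 1, in the data analysis section, lists 18 outcomes: 1 for fixation, 5 for prosaccade, 7 for antisaccade and 5 for memory-guided saccades.

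**The concern.** The test that was sized is not the test that will decide significance. The sample size assumes one comparison judged at 0.05. The analysis promises to judge several comparisons against a stricter standard. Unless a single outcome is exempt from the correction, and none is named, the 80% does not describe any comparison the study will make.

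Two later decisions depend on significance. The sample size section makes further recruitment depend on non-significant results, and the discriminant analysis of SWJ rate and anxiety goes ahead only if significant differences are found. If power per outcome is materially below 80%, a miss on a hypothesised outcome is more likely than the plan implies. With no primary outcome, the plan also does not say whose non-significance counts.

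**Working it through.** **Inputs.** From the sample size section: d = 0.8, alpha 0.05, power 80%, 26 per group. From the participants section: two groups of similar size, taken as 1:1. Sidedness is not stated. Two-sided is inferred because the two-sided independent-samples t-test gives 26 per group, whereas one-sided gives 21 per group and a paired test gives 15 pairs.

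**Formula.** With n per group, the t statistic has 2n − 2 degrees of freedom and noncentrality d × √(n/2). For n = 26 that is 50 degrees of freedom and 0.8 × √13 = 2.88. Power is the probability that the absolute value of this noncentral t exceeds the two-sided critical value at the alpha in force.

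**The plan's own figure.** At alpha 0.05, n = 26 gives 80.7% and n = 25 gives 79.1%. The minimum is therefore 26 per group, as stated.

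**Counting outcomes.**
- Fixation: SWJ rate (1).
- Prosaccade: gain, latency, peak velocity, anticipations, direction errors (5).
- Antisaccade: gain, latency, peak velocity, corrected errors, correction latency, uncorrected errors, anticipations (7).
- Memory-guided: gain, latency, peak velocity, inhibitory errors, directional errors (5).
- Total: 1 + 5 + 7 + 5 = 18. With four hypothesised, 18 − 4 = 14 remain.

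**Power per outcome under Bonferroni** (alpha = 0.05/m, d = 0.8, 26 per group):

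| Tests in family (m) | Alpha per test | Power per outcome | n per group for 80% |
|---|---|---|---|
| 1 | 0.05 | 80.7% | 26 |
| 2 | 0.025 | 71.6% | 31 |
| 3 | 0.0167 | 65.8% | 35 |
| 4 | 0.0125 | 61.7% | 37 |
| 18 | 0.0028 | 40.7% | 49 |

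With 26 per group, the effect detectable at 80% power is d = 0.92 over 3 tests, 0.96 over 4 and 1.11 over 18.

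**Other corrections.** These were simulated with 40,000 replicates per scenario. The correlation between outcomes (0 or 0.5) and the number of outcomes truly differing by d = 0.8 are assumptions, since the document gives neither.

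| Family | Truly differing | Holm, per outcome | Benjamini-Hochberg, per outcome |
|---|---|---|---|
| 18 | 1 | 41% | 41–42% |
| 18 | 4 | 42% | 53–54% |
| 18 | 18 | 50–52% | 74–78% |
| 4 | 4 | 71–73% | 76–78% |
| 3 | 3 | 74–76% | 77–78% |

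The highest value in any run was 78.4%. None of these three methods tests any single outcome at a threshold above 0.05, so 80.7% is a ceiling that a correction can only lower.

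**What 0.05 covers.** If 0.05 is the family-wise level, the correction operates and the table above applies. If it is the threshold for each test, the 80.7% stands but the correction has no effect. The chance of at least one false positive over 18 independent null outcomes would then be 1 − 0.95^18 = 60.3%.

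**The case against.** The strongest reply has four parts.

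1. *The size of the loss is not known.* The correction method and family are unnamed, and a journal article may leave both to a fuller document. This stands, and it limits the claim. A reader might infer that power is 41% and that each hypothesised difference is more likely missed than found. The document does not support that as a general statement. It needs Bonferroni, or something about as strict, across all of Table 1. Over three or four outcomes a true difference of d = 0.8 is still more likely found than missed. The mismatch does not depend on the method, however, because the calculation allows for no correction at all.

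2. *The two alpha statements are compatible.* A reader might see a contradiction between "Alpha will be set at 0.05 for all analyses" and the promised correction. There is none: adjusted p-values compared with 0.05, or a family-wise 0.05, satisfy both sentences. The wording is ambiguous, no more.

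3. *Power could mean finding at least one difference.* If four of the 18 outcomes truly differ by d = 0.8, Bonferroni over 18 finds at least one with probability 73–88%. With all four truly differing and Bonferroni over those four, the figure is 89–98%. This is a fair point about the broad primary aim. But the sample size section describes one t-test, not this kind of power, and the hypotheses name specific measures.

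4. *The study is exploratory and 26 is a minimum.* Both are true, and the planned correction addresses false positives in principle. Neither makes the stated 80% apply to the corrected tests. Recruiting more participants after a non-significant result is not a sizing for multiplicity.

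A reader might also conclude that 26 per group was miscalculated. It was not; it reproduces exactly for the question it answers.

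**Conclusion.** The point holds in this form: the 80% power belongs to one uncorrected two-sided test, and the plan commits to correcting across several outcomes without naming a primary one. Power per outcome at d = 0.8 with 26 per group is therefore below the stated figure. Under Bonferroni the shortfall is about 15 percentage points over three outcomes (80.7 − 65.8), 19 over four (80.7 − 61.7) and, near the worst case, 40 over all 18 (80.7 − 40.7). Holm and Benjamini-Hochberg lose less but stayed below 80% in every scenario run.

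This assumes a two-sided independent-samples test, equal groups, all 26 per group analysable, and d = 0.8 on each outcome that truly differs. The defect is one of alignment between sample size and analysis. It is not an arithmetic error, and the two statements about alpha do not conflict.

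**What to change.** Change the wording in the sample size and statistical analysis sections:

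- **Primary family.** Name SWJ rate, prosaccade latency, antisaccade latency and memory-guided inhibitory error rate as the primary family, tested with Holm at family-wise 0.05. Alternatively, name one primary outcome tested at 0.05, in which case the existing 80.7% stands for that outcome.
- **Remaining outcomes.** Label the other Table 1 outcomes (14 if the family has four) exploratory and report them with confidence intervals.
- **Alpha.** State that 0.05 is family-wise for the primary family.
- **Power.** With the four-outcome family, restate power at 26 per group as about 62% per primary outcome at the strictest Holm step, and about 71–73% if all four truly differ by d = 0.8.

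No participants need be added. The cost is a less favourable stated power or, with a single primary outcome, treating the other hypothesised outcomes as secondary. If the sponsor wishes to keep 80% at the strictest step for four outcomes, that would take 37 per group, before any allowance for excluded recordings.
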